### 2.2 Participant eligibility

#### 2.2.1 Age range justification

We decided to acquire a medium-sized Trexo, which fits children aged 3–6 years old (height and weight requirements). We aim to work with children at an early intervention point where there is still considerable developmental potential for change and capitalize on the developing brain’s neuroplastic nature (Novak et al., 2017). According to GMFM Motor Growth Curves for children with CP (GMFCS IV) there is still potential for motor gains for children under the age of 6 (Rosenbaum et al., 2002).

#### 2.2.2 Inclusion criteria

(a) Age 3–6 years inclusive at the time of receiving the study invitation; (b) mobility impairment caused by a non-progressive neuromuscular disorder, classified as **GMFCS Level IV** or equivalent: uses a wheelchair (pushed by others or powered) most of the time, and walking is very limited even with use of assistive devices (Palisano et al., 2008) and able to sit on chair but need adaptive seating for trunk control and to maximize hand function, can move in and out of chair with assistance from an adult or a stable surface to push or pull up on with their arms, can walk no more than short distances with a maximum support walker/stepping device and caregiver assistance (Rosenbaum et al., 2008); (c) weight: 20–100 lbs to fit within our medium size Trexo; (d) leg length with specific measurement of the hip to the knee of 17–27 cm and knee to floor of 18–32 cm while wearing shoes; (e) able to indicate pain, fear, or discomfort verbally or non-verbally; (f) able to respond to one or two-step commands; and (g) at least 2 months after any lower limb Botulinum Toxin injections. Children may have a maximum support manual walker (e.g., a supported stepping device such as the Rifton Pacer Gait Trainer^1^ - a wheeled “walking” frame or support walker that provides trunk and pelvic support and has a soft strap or solid seat and arm support as needed) that they use as their gait device at home/school, but this will not be necessary to be eligible to participate in the study.

#### 2.2.3 Exclusion criteria

(a) As per the Trexo Plus Operations manual (Trexo Robotics, 2022), unless cleared by study physician: knee flexion contracture > 20°; knee valgus > 40°; hip extension < −10°; hip subluxation > 40%; (b) dynamic spasticity or behavioral concerns that interfere with the use of the Trexo; (c) weight-bearing restrictions (d) osteogenesis imperfecta; (e) orthopedic surgery within the last 6 months (if muscle) or 12 months (if bone), or planned within the next 6 months; (f) seizure disorder that’s not controlled by medication; (g) unable to pass MRI screening; (h) involved in another interventional study (reviewed on a case-by-case basis); (i) received robotic exoskeleton training in the past; (j) neurological, respiratory, cardiac, and orthopedic medical conditions that would restrict physical activity as reported by parents; (k) open skin lesions or vascular disorders of the lower extremities; and (l) not able to discontinue Botulinum Toxin injections for 6-week period during study intervention.

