**FIGURE 1 F1:**
[figure not shown]
Flow chart of study visits and timeline, reflecting O_0_ X O_1_ O_2_ design.

**TABLE 1 T1:** Research team member designations and corresponding roles in the study.

Designation	Role
Principal investigators	Responsible for study oversight and adverse event management.
Study researchers	Non-PT team members that are responsible for coordinating recruitment, scheduling, non-PT data collection, and data analysis.
Study physician	Center-affiliated pediatrician that helps with diagnostic expertise, recruitment, eligibility, and adverse event management.
Treating PTs/PTAs	Physiotherapy team members that are Trexo-trained and complete the 12 Trexo (twice weekly) intervention sessions.
PT assessors	Independent PTs (different from treating PTs) that complete the physical screening and motor/functional assessments.
Study interviewer	Independent team member that hosts all Zoom-based interviews.
MRI technician	Centre-affiliated technician that operates MRI scanner.

During ‘**O’ phases (pre/post intervention)**, participants will do their usual physiotherapy regimen (with their usual assistive device, where applicable) and associated home program, and will undergo the set of study assessments (gross motor/functional assessments and neuroimaging) in this approximately 2–3-week period pre- and post-Trexo use (Phase X). One-month post O_1_, participants will have one final motor/functional assessment and neuroimaging visit (O_2_). They will continue with their usual physiotherapy regimen during the month between O_1_ and O_2_.

**Intervention ‘X’ phase** will consist of the Trexo physiotherapy block: physiotherapy sessions twice weekly (30-min sessions excluding initial set-up time) for 6 weeks provided by a study-trained PT/Physiotherapist Assistant (PTA) team within a goal-based training program that is grounded in motor learning principles. Trexo physiotherapy will be integrated within a school-based program for half of the study cohort (*n* = 5), and within an outpatient program for the other half (*n* = 5). Each child will receive 1–2 acclimatization/fitting sessions in the Trexo before starting physiotherapy sessions. Walking tests and muscle recordings at the start and end of this phase will be done in the Trexo and in the child’s usual non-robotic wheeled walker (if they use one) for comparison and for assessment of potential carryover effects from Trexo use to their wheeled walker.

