#### 2.3.2 Physical screening

A PT assessor will perform the child’s in-person physical screening following receipt of written informed consent from the parent, and will document the following: height (body and leg lengths), range of motion, orthopedic/medical suitability, cognitive ability to participate in physiotherapy, current home program, method of communicating discomfort or pain, and parent’s willingness to commit to the treatment frequency and to refrain from commencing other new therapies during O_0_, X, and O_1_ phases the study. The study physician will review the results of this screening and confirm the child’s eligibility to proceed with the study.

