#### 2.6.1 Gross motor skills

The *Gross Motor Function Measure* (GMFM-88; Russell et al., 2000) will be administered by an independent PT assessor during the motor/functional assessment at baseline and immediately post-intervention. It will also be used 1-month post-intervention to gauge maintenance/progression of any functional gains. PT assessors will be trained on the GMFM-88 and all other PT assessment measures by the study’s co-principal investigator prior to their first study assessment. All PTs will already have extensive clinical experience administering the GMFM with children with CP, and variable experience with the other measures. The full 88-item version of the GMFM will be used as it more comprehensively captures a range of abilities in its lowest dimensions (Lie/Roll and Sit) than the abbreviated GMFM-66. This will be important as better trunk and head control are anticipated to be goals and potential outcomes associated with Trexo use in children in GMFCS Level IV. The GMFM-88 testing will be captured on video to enable post-assessment review by PTs. Pre/post change scores will be calculated with descriptive statistics representing results of the group. The GMFM has excellent test-retest reliability (Bjornson et al., 1998), and responsiveness to change (Vos-Vromans et al., 2005).

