#### 2.6.3 Neuroimaging

Awake magnetic resonance imaging (MRI) head scanning will be done in the Siemens Prisma MAGNETOM 3-Tesla MRI scanner with a 36-channel head coil at Holland Bloorview Kids Rehabilitation Hospital (Figure 4). If tolerated, these will be done at baseline and immediately post-intervention, with an option for a third scan 1-month post-intervention. Prior to the baseline scan, families will be provided with MRI resources intended to prepare and educate them for an awake scan with their child. Resources include a child-friendly MRI explanation book, video links to a tour of the center’s MRI suite, links to MRI cartoons, links to MRI sound samples, and a link to the resting state fMRI video. This is meant to ease any apprehension or stress associated with the MRI process.

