#### 2.7.1 Body structure and function

*Passive range of motion* (ROM) of selected movements (hip flexion contracture; hip abduction; popliteal angle; knee flexion contracture; ankle dorsiflexion with knee flexed or extended), and evaluation of resting and dynamic spasticity as measured by the *Tardieu Scale* (Scholtes et al., 2006) at knee and ankle (hip adductors, hamstrings, gastrocnemius with knee flexed and extended) will be conducted at all functional assessment timepoints. This is important to establish at baseline (excerpted from screening session data where ROM eligibility was confirmed) to monitor adverse events, and permit evaluation of changes in ROM associated with Trexo use.

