### 2.11 Data analysis

#### 2.11.1 Quantitative data analysis

*Feasibility/safety/acceptability indicators* (section “2.5 Feasibility and acceptability indicators”) will be summarized for each child’s sessions and the group descriptive statistics will be compared to *a priori* target values.

*Motor/functional assessment measures and functional priority goals* will have total/dimension scores summarized via descriptive statistics. Paired *t*-tests or non-parametric equivalents will be conducted for baseline and post-intervention time points for the co-primary measures (GMFM-88 and COPM goals), and then with each of the secondary outcomes. Correlational analyses (Pearson’s r) will also be undertaken to investigate associations between primary and secondary outcomes or with MRI results. Each clinical measure will be graphically inspected for any patterns from baseline to the optional 1-month post-intervention timepoint. For a subsample of children (undetermined subgroup ‘n’ at this point), comparisons will also be made between walking performance in the child’s regular walker and the Trexo at baseline and post-intervention.

*MRI scans* will be processed with Freesurfer Software (surfer.nmr.mgh.harvard.edu), employing a longitudinal pipeline. Automated segmentation of structural T1-weighted images will be performed, followed by quality control steps to ensure image clarity. Any neuroimaging data with excessive motion artifact will be excluded from the study. Regions of interest (ROI) will be selected based on brain areas that are most associated with gait, motor function, and motor learning. From T1 anatomical data, mean cortical thickness per brain region, and white and gray matter volumes will be calculated. Diffusion data will be used to identify and reconstruct relevant white matter tracts as well as derive DKI and DTI mean metric maps, kurtosis fractional anisotropy (FA) values, and mean kurtosis (MK), as outcome measures. From the fMRI data, ROI-specific time courses of the BOLD signal will be computed by averaging time courses across voxels within each ROI. fMRI outcome measures will include functional connectivity (FC) correlation matrices and a structural-decoupling index.

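### The Botulinum Toxin condition covers only the 6-week block, so a repeat injection between the paired O0 and O1 readings is not clearly barred (minor)

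*Protocol article*

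**What the plan says.** Three rules in the protocol article bear on Botulinum Toxin or on other treatment during the study.

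- Inclusion (g) in 2.2.2 requires that a child be "at least 2 months after any lower limb Botulinum Toxin injections". It looks backward and gives no reference date.
- Exclusion (l) in 2.2.3 removes a child who is "not able to discontinue Botulinum Toxin injections for 6-week period during study intervention".
- Section 2.3.2 records the parent's willingness to "refrain from commencing other new therapies during O_0_, X, and O_1_ phases the study".

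On timing, 2.1 places the study assessments "in this approximately 2–3-week period pre- and post-Trexo use", and phase X itself lasts 6 weeks. Section 2.6.1 puts the GMFM-88 "during the motor/functional assessment at baseline and immediately post-intervention", and 2.6.3 says of the MRI scans that "these will be done at baseline and immediately post-intervention".

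On analysis, 2.11.1 plans paired tests for "baseline and post-intervention time points for the co-primary measures (GMFM-88 and COPM goals), and then with each of the secondary outcomes". Table 2 lists ROM and Tardieu spasticity among the secondary outcomes, at O0, O1 and O2, and its footnote places them at the motor/functional assessment visit. Section 2.7.1 also schedules them at every functional assessment but says of the baseline: "This is important to establish at baseline (excerpted from screening session data where ROM eligibility was confirmed) to monitor adverse events".

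**The concern.** In a pre/post study without a control group, any treatment given between the two readings is mixed with the treatment under study. The period to protect is the interval between the readings, not the treatment block alone. The pledge in 2.3.2 follows that logic by running over O0, X and O1; the toxin condition does not.

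A child whose injection was deferred for the block could be injected after the last session and before O1, or between the O0 assessment and the start of X. ROM and Tardieu are the most directly exposed outcomes. If toxin increases range or lowers spasticity (an assumption, since the protocol gives no toxin effect), the change would be read as a Trexo benefit. Because ROM also serves to monitor adverse events, it could hide a loss of range.

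The ROM baseline raises a separate, smaller matter. The screening reading is the one against which the knee-contracture and hip-extension limits were applied. Using it again as the baseline invites regression to the mean in those movements.

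**Working it through.** The plan states no figure that needs reproducing. The check sets the windows side by side and then gauges the possible size.

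**1. Windows (from the documents)**
- No-toxin condition: 6 weeks, equal to X.
- After X: 0 weeks if O1 is truly immediate, otherwise up to 2–3 weeks. As a share of the time from the start of X to O1, the upper end is 2/(6+2) = 25% to 3/(6+3) = 33%. This is a worst-case share of time, not a risk of injection.
- Before X: up to 2–3 weeks between the O0 assessment and X.
- Whole interval between paired readings: at most 2+6+2 = 10 to 3+6+3 = 12 weeks, of which 6 are covered.

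**2. Does another rule close the gap?**
- Inclusion (g) bars nothing after its reference date. If that date were the start of X, it would cover the interval before X; the text does not say.
- The 2.3.2 pledge would cover a first-ever injection. A repeat in a child already treated is not clearly new.

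**3. Possible size for ROM (all inputs assumed)**
Gain per injected child g = 5–15°; fraction present by O1 f = 25–100%; k = 1 or 2 injected children of n = 10; measurement-error SD s = 3–5°.
- Shift in mean change = k·g·f/10. For k = 1: 5×0.25/10 = 0.1° to 15×1/10 = 1.5°. For k = 2: 0.3° to 3.0°.
- Standard error of mean change from measurement error alone = √2·s/√10 = 1.3° (s = 3) to 2.2° (s = 5).
- Simulated chance of a favourable paired t-test (two-sided 0.05, no true effect, change SD √2·s, 100,000 trials):

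| Injected children | f = 25% | f = 100% |
|---|---|---|
| 0 | 2.5% | 2.5% |
| 1 | about 3–4% | about 3–4% |
| 2 | about 3–6% | about 5–9% |

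- Limit for one child's change = 1.96·√2·s = 8.3° (s = 3) or 13.9° (s = 5).

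**4. ROM baseline (all inputs assumed except the 20° limit)**
True knee contracture is normal with mean μ and SD 6°, and a child is kept if the screening reading is at most 20°. With c = (20 − μ)/√(36 + s²), the expected apparent worsening at an unselected later reading is s²/√(36 + s²) · φ(c)/Φ(c).
- μ = 8: 0.1° (s = 3), 0.4° (s = 5).
- μ = 12: 0.3° (s = 3), 0.9° (s = 5).
- If the study physician clears half of the children over the limit: 0.1–0.4° over the same inputs.

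**The case against.** The strongest reply is that the text nearly closes the gap after X. The GMFM-88 is done immediately post-intervention, ROM and Tardieu belong to the same visit, and the MRI is timed likewise. The 2–3 weeks in 2.1 is a window for the whole set of assessments, not a stated delay. This stands: exposure after X may be close to zero, although the protocol allows more.

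Second, the 2.3.2 pledge already spans O0 to O1, and a reader could take it to include toxin. This stands in part. The wording is ambiguous rather than permissive, so one should not infer that the protocol allows or plans injections before O1. The documents also do not show that any child would be due for one.

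Third, every effect input above is assumed. This stands in full. A reader might infer that the group result is materially biased, but one injected child hardly moves the test, and 5–9% needs two children with the full gain already present. A reader might also infer that an injected child would be read as a responder. A 10° gain exceeds the limit only at error SD 3°, not at 5°, and the plan has no child-level ROM response rule.

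Fourth, this is a feasibility study of 10 children, ROM and Tardieu are secondary, and no feasibility target is a ROM or Tardieu score. This also stands and limits the weight of the point.

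On the ROM baseline, Table 1 gives screening and assessment to the same PT assessor role, so no difference between assessors can be claimed. Figure 1 is not shown, so screening may lie close to O0.

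**Conclusion.** The point holds as a minor one. The no-toxin condition stops at the edges of the intervention, while the paired readings lie outside it by up to about 2–3 weeks on each side, possibly near zero after X. No other rule clearly bars a repeat injection in those intervals, and the design cannot separate its effect from that of Trexo. The exposure is mainly in ROM and Tardieu.

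The size cannot be derived from the documents. Under the assumed inputs, one injected child takes the chance of a favourable group test from 2.5% to about 3–4%. Two take it to about 3–6% with a quarter of the gain present, or 5–9% with all of it. The documents do not support a claim that the study's main conclusions are at risk.

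The ROM baseline is a genuine inconsistency between 2.7.1 and Table 2. Its expected effect is small, about 0.1–0.9° of apparent knee worsening under assumed inputs.

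**What to change.** - Reword exclusion (l), or name Botulinum Toxin in the 2.3.2 pledge, so that no injection, first or repeat, is given between the O0 assessment and completion of the O1 motor/functional assessment.
- Schedule O0 shortly before X and O1 promptly after it, so that the added deferral is short.
- Record any injection given in that window anyway, and show ROM and Tardieu change with and without that child.
- In 2.7.1, compute ROM change from the O0 reading and keep the screening value for eligibility only.

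The cost is a toxin deferral longer by at most about 2–3 weeks on each side, and less with prompt assessments. A fixed deferral of 10–12 weeks for every treated child is not needed; it would be a heavier clinical burden and could deter families, against an enrolment target of 80%. The ROM change uses an examination that Table 2 already schedules. No visit is added.

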#### 2.2.4 Sample size justification

The planned sample size of 10 children for this feasibility study will be sufficient to give an initial group picture through descriptive statistics and summary graphs of feasibility indicators and quantitative outcomes. This aligns with other quantitative pediatric therapy technology-based intervention studies that have successfully provided meaningful feasibility study results with 4 to 20 participants: (Richards et al., 1997; Wallen et al., 2008; Weightman et al., 2011; Radtka et al., 2013). This sample size will also elucidate how a single robotic assistive device may be shared (i.e., fitting adaptations to support use) among multiple children for use as a physiotherapy intervention within a center.

For the qualitative user perspective data, there is no agreed-upon sample size to achieve saturation in qualitative research (Saunders et al., 2018), instead depending collectively on sample homogeneity, interaction quality, and theoretical framework (Malterud et al., 2016).

Previous qualitative descriptive studies with children, parents, or clinicians reporting on user experiences of applying new technology or outcome measures have produced meaningful results with samples of 5 to 13 participants (Rich et al., 2014; Beveridge et al., 2015; Phelan et al., 2015; Kahlon et al., 2019; Vaughan-Graham et al., 2020; Giancolo et al., 2022; Hadj-Moussa et al., 2022; Torchia et al., 2023).

### 2.3 Participant enrolment

#### 2.3.1 Invitation letters from circle of care

Pediatricians, PTs, and clinic staff affiliated with the hospital-based outpatient program and the school integrated education therapy program will share study invitation letters with parents of the children on their caseload who meet the main eligibility criteria. Interested parents will have an initial phone conversation with the study’s research coordinator who will provide them with full details on the study, and if they are interested in moving ahead, will then review the study’s basic eligibility questions. If these criteria are met, they will be added to a candidate list that will be capped by a predetermined date deadline. If the list exceeds capacity, names will be drawn by a random number system (randomizer.org) to schedule an in-person physical screening visit to confirm eligibility.

#### 2.3.2 Physical screening

A PT assessor will perform the child’s in-person physical screening following receipt of written informed consent from the parent, and will document the following: height (body and leg lengths), range of motion, orthopedic/medical suitability, cognitive ability to participate in physiotherapy, current home program, method of communicating discomfort or pain, and parent’s willingness to commit to the treatment frequency and to refrain from commencing other new therapies during O_0_, X, and O_1_ phases the study. The study physician will review the results of this screening and confirm the child’s eligibility to proceed with the study.

#### 2.3.3 Informed consent

Informed consent will be obtained from: child’s parent, child (assent; contingent on capacity assessment determination prior to the consent session) for the Trexo intervention and associated assessments, PT/PTAs for study interviews (post child’s Trexo use), and parent for study interviews (pre and post child’s Trexo use). Consent for neuroimaging will be obtained separately.

### 2.4 Study intervention

#### 2.4.1 Trexo plus pediatric exoskeleton

The Trexo Plus lower limb exoskeleton (Figure 2) comprises powered orthotic legs which work cohesively within a Rifton Pacer wheeled walker that has been adapted to accommodate the exoskeleton attached to its frame. The Trexo’s robotic legs are a multi-joint system with two actuated degrees of freedom per lower limb for hip flexion-extension and knee flexion-extension. This design makes the device responsive to the child’s ability to initiate steps, and able to provide proportional support needed for leg movement as provided through more mechanically active “endurance mode” or more passive “strength mode”. It can also be used in “standing mode” for upright activity facilitation. Trexo settings are adjusted via a user-friendly tablet interface that monitors walking time, step count, and initiation (Trexo Robotics, 2022). The Trexo requires a person outside of the user to facilitate steering and turning via the guide bar attached to the Rifton frame. For this study protocol, the Trexo robotic legs will be oriented outward (facing out of the open side of the Rifton Pacer frame), to maximize the child’s hands-free participation during physiotherapy (Tao et al., 2020).

